### Outcome measures

#### Primary outcomes

Primary outcomes include muscle activation sequence (Hodges, 2001; Suehiro et al., 2015), iEMG, RMS, and MF, generated from sEMG (Thomas et al., 2007; Aruin et al., 2015; Aruin, 2016). The EMG data will be gathered from the probe on the surface of deltoids, lumbar multifidus, transverse abdominis muscle (TrA), erector spinae muscle, gluteus maximus, and hamstrings. Each channel’s interelectrode distance will be 10 mm.

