#### Secondary outcomes

The JOA Score (Oshima et al., 2020) and the McGill Pain Questionnaire (MPQ) (Main, 2016) are the secondary outcomes. JOA Score takes into account bladder function, daily activity, clinical indicators and subjective complaints, with the lowest score of 6 and the highest score of 29. Better functioning conditions are indicated by higher overall scores. MPQ is made up of 15 carefully chosen words, comprising 4 emotional and 11 sensory words. Each item is given a number from 0 to 3, with a higher score denotes a severer symptom (Choi et al., 2015). Biomarkers like substance P (Bhatia, 2015) and beta-endorphin (Choi and Lee, 2019) will also be tested.

All the primary and secondary outcomes will be assessed before and 1 week after treatment.

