### Statistical analysis

Test-retest reliability and content consistency reliability will be used to gauge the scale’s dependability (test-retest reliability). Cronbach’s coefficient is the most often used measure of internal consistency reliability. The better the homogeneity, the higher the Cronbach’s alpha coefficient. If the scale’s consistency is greater than 0.8, it is considered to be good, and if it is greater than 0.7, it is considered to be acceptable.

SPSS version 20.0 (SPSS Inc., Chicago, IL, USA) will be used for all of the analysis. The significance threshold will be set at 0.05, and the confidence interval will be 95%. The χ^2^ will be used to analyze categorical data. For continuous variables, mean ± SD will be recorded by using ANOVA test if they were normally distributed, or the median with interquartile range will be shown with Kruskal–Wallis H test. The Bonferroni correction and Tukey *post-hoc* test (for ANOVA) will be used to handle multiple comparisons (for Kruskal–Wallis). The Chi-square test will be used to verify the classification count data. Two-tailed test will be used in this study. The difference will be regarded as statistically significant when *P* < 0.05.

To handle missing data, we will evaluate the underlying cause, employ an imputation adjustment approach, and do a last observation carried forward analysis. Following the primary analysis, a sensitivity analysis will be carried out to determine the effect of missing data on the trial outcomes by contrasting the findings from the per-protocol analysis and the intention to treat analysis. Also planned are subgroup analysis by the center.

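### A normality check on the observed data decides whether each continuous outcome is compared by means or by ranks, and the rank branch as written yields no between-arm estimate with an interval

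*Protocol article*

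**What the plan says.** The rule is in the protocol article, Statistical analysis. Continuous variables are to be summarised and tested "by using ANOVA test if they were normally distributed, or the median with interquartile range will be shown with Kruskal–Wallis H test". No normality test, cut-off or unit of checking is named, and no outcome is assigned to a branch in advance.

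The same paragraph states "The significance threshold will be set at 0.05, and the confidence interval will be 95" (per cent), without saying what the interval is for. Decisions rest on two-sided P values: "Two-tailed test will be used in this study", with 0.05 as the cut-off.

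The post-hoc sentence names the Bonferroni correction and Tukey's procedure together and then reads "test (for ANOVA) will be used to handle multiple comparisons (for Kruskal–Wallis", so the bracketed labels do not line up with the two methods.

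The rule applies to these outcomes:
- **Primary outcomes:** "Primary outcomes include muscle activation sequence", iEMG, RMS and MF, recorded from six muscle sites.
- **JOA:** a bounded score, "with the lowest score of 6 and the highest score of 29".
- **MPQ:** 15 items, of which "Each item is given a number from 0 to 3", so 0 to 15 × 3 = 45.
- **Biomarkers:** substance P and beta-endorphin.

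Study design expects improvement in pain and lumbar function no smaller with Qigong than in either other group, and the Discussion repeats this.

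**The concern.** ANOVA and Kruskal–Wallis answer different questions. The first compares means. The second compares rank distributions, and its usual output is one overall P value. If the data choose between them, nobody can say before the analysis what will be compared for a given outcome, and the same EMG measure may be compared by means in one muscle and by ranks in the next.

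The practical loss is on the rank branch. Group medians with interquartile ranges describe each arm. They do not estimate the difference between arms or show how precisely it is known. A non-significant Kruskal–Wallis result cannot show that Qigong is at least as good as motor control exercise or celecoxib. That takes an estimated difference and its interval.

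**Working it through.** The plan gives no figure for how often outcomes would change branch, so there is none to reproduce. The check asks how the rule behaves at the planned size.

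**Inputs from the documents**
- 28 per arm, three arms (Sample size; Allocation). With the stated 10% dropout, 84 × 0.9 = 75.6, or about 25 per arm.
- Significance level 0.05 (Statistical analysis).
- JOA limited to 6–29; MPQ limited to 0–45 (Secondary outcomes).

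**Assumptions, not in the documents**
- The check is Shapiro–Wilk at 5%. In one version any rejection in any arm sends the outcome to Kruskal–Wallis (per-arm check). In the other the test is applied once to pooled residuals (residual check).
- All distribution shapes, means and SDs below.

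**Step 1. Exactly normal data.** With three independent checks at 5%, the chance of at least one false rejection is 1 − 0.95³ = 0.143, or 14%. A single residual check gives about 5%. Simulation gives about 14–16% and 4–6%.

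**Step 2. Other shapes.** Simulated share sent to Kruskal–Wallis, 28 per arm:

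| Assumed data | Per-arm check | Residual check |
|---|---|---|
| Log-normal, log-SD 0.2 | 43–46% | not tabulated |
| Log-normal, log-SD 0.3 | 70–72% | 77% |
| Log-normal, log-SD 0.5 | 97% | 99% |
| JOA-like, mean 20, SD 4 | 17–18% | 5% |
| JOA-like, mean 22, SD 3 | 25% | 8% |
| JOA-like, mean 24, SD 3 | 34% | 25% |
| JOA-like, mean 24, SD 4 | 70% | 77% |
| JOA-like, mean 26, SD 3 | 96–97% | 97–98% |
| MPQ-like, mean 10, SD 6, normal cut at 0 | 20–22% | not tabulated |
| MPQ-like, mean 10, SD 6, gamma | 92–93% | not tabulated |

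Ranges within a cell are repeat simulations. At 25 per arm the per-arm rates are slightly lower, for example 68% at log-SD 0.3 and 95% at log-SD 0.5.

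**Step 3. Two muscles with the same distribution.** If each switches with probability p, independently, they receive different tests with probability 2p(1 − p):
- p = 0.43: 2 × 0.43 × 0.57 = 0.49
- p = 0.70: 2 × 0.70 × 0.30 = 0.42
- p = 0.97: 2 × 0.97 × 0.03 = 0.06

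The expression cannot exceed 0.50. Muscles measured in the same participants are correlated. With correlation 0.8 and log-SD 0.2 the simulated figure falls to 36–40%.

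**Step 4. Error rates.** The type I error of the two-stage rule was 0.041–0.060 across the scenarios. For log-normal data with a shift of 0.75 log-SD, its power was 79–82%, against 82% for ANOVA on the log scale. Power was not compared for JOA- or MPQ-like scores.

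**The case against.** The strongest reply is that the rule is stated in advance, keeps type I error near nominal, and costs little power. The name of the normality check is a detail an analysis plan would supply, and nothing forbids reporting an effect estimate beside either test. This largely stands for error control and for the unnamed check. It does not answer the central point: the article itself fixes a rule under which the data choose the compared quantity, and it specifies the output of the rank branch as medians, interquartile ranges and a test.

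Several stronger readings are tempting and are not supported:
- **A broken promise of intervals.** A reader might infer that a 95% interval is promised for every treatment effect. The text sets a confidence level and names no quantity. It names no effect estimate on the ANOVA branch either, although mean differences with intervals follow readily there.
- **Most outcomes will end on ranks.** The documents give no distributions. The JOA result runs from close to the false-rejection rate to nearly every trial, depending on how near the scores lie to the ceiling. MF and activation time may stay mostly with ANOVA.
- **Muscles will disagree about half the time.** That is near the mathematical maximum and needs independent muscles. Where nearly everything switches, disagreement almost disappears.
- **Tukey will be applied to data judged non-normal.** The post-hoc sentence reads as a misplaced bracket. Tukey for ANOVA and Bonferroni for Kruskal–Wallis is the evident meaning.

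**Conclusion.** The point holds, with limits. The data decide for each continuous outcome whether means or ranks are compared, and the rank branch as written leaves no between-arm difference with an interval. That does not fit a trial whose stated expectation is at-least-equal improvement.

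The frequency is conditional on assumed shapes and an assumed check. With 28 per arm and Shapiro–Wilk at 5%:
- Normal data: about 4–14%.
- Log-normal data, log-SD 0.2–0.5: 43–97%.
- JOA-like scores, assumed means 20–26: 17–97% with the per-arm check, 5–98% with the residual check.
- MPQ-like scores: 22–92%, depending on shape.

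A reader might infer an inflated false-positive rate, but the simulations do not show one. The harm is to estimation and to comparability across muscles. The post-hoc sentence needs only a wording correction.

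**What to change.** 1. Delete the condition on normality and prespecify one linear model per continuous outcome, adjusted for the baseline value that is already collected, with heteroscedasticity-robust standard errors.
2. Use the original scale for JOA, MPQ, activation time and MF, and the log scale for iEMG, RMS, substance P and beta-endorphin.
3. Report the arm differences, or geometric-mean ratios for the log-scale outcomes, with 95% confidence intervals adjusted for the three pairwise comparisons.
4. Keep Kruskal–Wallis with Bonferroni-corrected pairwise comparisons as a supportive analysis only.
5. Reword the post-hoc sentence so that Tukey is attached to ANOVA and Bonferroni to Kruskal–Wallis.

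This covers continuous outcomes, including activation times. If the order of muscle activation is analysed as an order, it needs its own summary.

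The cost is a few reworded sentences and slightly more analysis work, with no new data. Readers will see ratios rather than raw differences for the log-scale outcomes. No power loss of note was seen for log-normal data, but this was not checked for JOA and MPQ.

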## Strengths and weaknesses of this research

1.The purpose of this study protocol is to conduct the first-ever single-blinded, randomized controlled trial to assess the effectiveness and potential mechanism of Mawangdui-Guidance Qigong Exercise for CNLBP.2.Biological markers and EMG data are included in the primary and secondary outcomes. There has been no agreement achieved despite numerous EMG investigations that attempted to disclose the CNLBP with muscle activity sequence mechanism. Beta-endorphin levels and substance P, which are quick, safe, and effective markers to gauge pain relief will be tested.3.Participants are limited by ages between 20 and 39 for easily identification of specific chronic LBP or CNLBP, further researches on differences of various ages are needed.4.This is a single-center RCT with limited sample size, multi-center experiments can be conducted to get reproducible and stable results in the future.5.The treatment duration keeps 4 weeks without longer-term observation, we plan to conduct a follow-up at the 8th and 12th weeks by phone after the trial finished.

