## Methods and design

### Study design

This study is a randomized, single-blinded clinical trial to investigate the effectiveness of Mawangdui-Guidance Qigong Exercise for CNLBP. This study will be conducted at the Hospital of Chengdu University of Traditional Chinese Medicine (CDUTCM). For the duration of the 4-week course of therapy, 84 participants who meet the trial criteria will be assigned at random to the Mawangdui-Guidance Qigong Exercise group, the MCE group, or the medicine group. Participants in Qigong group and MCE group will receive different types of exercise therapies under the supervision of different professional coaches. Others in the medicine group will be given celecoxib orally on a regular basis. EMG data, including muscle activation time, iEMGs, root mean square value (RMS) and median frequency (MF), will be the main outcomes. The Japanese Orthopedic Association (JOA) Score, the Mcgill Pain Questionnaire (MPQ), beta-endorphin, and substance P will be the secondary outcomes. All outcomes will be evaluated at the start of treatment and 4 weeks later. We think Mawangdui-Guidance Qigong Exercise can produce an improvement in pain and lumbar function that is equal to or greater than what the other two groups can.

The study is approved by the Sichuan Regional Ethics Review Committee on Traditional Chinese Medicine (Approval No. 2020KL-067) and registered with China Clinical Trial Center Registration (ChiCTR2000041080). The implementation follows the principles of the Declaration of Helsinki (Version Edinburgh 2000). The SPIRIT guidelines and CONSORT flow diagram will be followed in this investigation. The whole study design will be illustrated as a flow chart in Figure 1 and the process timetable will be shown in Table 1.

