### Sample size

By utilizing a two-sided 0.05 level *t*-test with >95% power and assuming a 10% dropout rate, the sample size was estimated to demonstrate the influence of the target muscles on MF (Zhou, 2018). To detect a target effect size of 0.44 (GPower 3.1) with 28 participants in each group, a sample size of 84 participants is needed.

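### At week 4, last observation carried forward amounts to baseline carried forward, and the per-protocol versus intention-to-treat contrast does not vary the missing-data assumption

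*Protocol article*

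**What the plan says.** **Schedule.** Study design states: "All outcomes will be evaluated at the start of treatment and 4 weeks later". The section on secondary outcomes states: "All the primary and secondary outcomes will be assessed before and 1 week after treatment". The two differ on timing, but both give one assessment before treatment and one after. Table 1 agrees: EMG and laboratory tests are ticked only at week −1 and week 4. JOA and MPQ are ticked at those weeks and again at weeks 8 and 12, which fits the statement that "we plan to conduct a follow-up at the 8th and 12th weeks by phone after the trial finished".

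**Primary outcomes.** These are all surface-EMG measures ("Primary outcomes include muscle activation sequence", with iEMG, RMS and MF).

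**Missing data.** The Statistical analysis section lists three steps: look into the cause, then "employ an imputation adjustment approach, and do a last observation carried forward analysis". The imputation approach is not defined there. The sensitivity analysis for the effect of missing data is to be made "by contrasting the findings from the per-protocol analysis and the intention to treat analysis".

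**Test and planning rate.** Continuous outcomes are compared by one-way ANOVA ("mean ± SD will be recorded by using ANOVA test if they were normally distributed") or Kruskal–Wallis. The sample size assumes a "two-sided 0.05 level *t*-test with >95% power and assuming a 10% dropout rate".

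**The concern.** LOCF needs an earlier on-treatment value to carry. Here there is none: for anyone without week-4 data the last observation is the pre-treatment one. The method then asserts that this person did not change at all, and the ANOVA treats that value as a real measurement. If one arm loses more participants than another, equally effective treatments look different. If the arms lose the same share, a true difference shrinks. Dilution matters here because the investigators expect Qigong to do as well as or better than the comparators, and dilution makes arms look alike.

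The stated safeguard does not address this directly. Moving from intention to treat to per-protocol changes who is analysed. It does not change what is assumed about values nobody observed, so agreement between the two could be read as reassurance about missing data that it cannot give.

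**Working it through.** **1. What LOCF inserts at week 4**

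| Outcome | Assessments up to week 4 | Value carried if week 4 is missing |
|---|---|---|
| EMG measures (primary) | week −1, week 4 | baseline |
| Substance P, beta-endorphin | week −1, week 4 | baseline |
| JOA, MPQ | week −1, week 4 | baseline |

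The later JOA and MPQ contacts at weeks 8 and 12 cannot supply an earlier value for week 4. A gap at week 8 or 12 could be filled from week 4, which is a separate matter.

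**2. Expected bias**

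Let arm A have true mean improvement μA and dropout dA, and likewise for arm B, with dropout unrelated to outcome. Scoring dropouts as zero change gives

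expected difference = (1 − dA)μA − (1 − dB)μB.

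If μA = μB = μ, this is (dB − dA)μ, although the true difference is zero.

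- 5% v 15%, μ = 1 SD: 0.10 × 1 = 0.10 SD.
- 5% v 15%, μ = 0.5 SD: 0.10 × 0.5 = 0.05 SD.
- 0% v 20%, μ = 1 SD: 0.20 × 1 = 0.20 SD.
- 0% v 20%, μ = 1.5 SD: 0.20 × 1.5 = 0.30 SD.
- 10% in both arms, true difference 0.44 SD: 0.90 × 0.44 = 0.396 SD.

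The 0.44 is the target effect size under Sample size. It is used here as a standardised mean difference only to show scale; the article does not say which index it is, and the point does not depend on it.

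**3. Effect on the test**

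The simulation used 28 per arm, baseline to follow-up correlation 0.5, random dropout, baseline substituted for missing values, and a test on the follow-up value at two-sided 0.05. Only the 28 per arm and the 0.05 come from the article. The correlation, the improvement and the dropout splits are assumptions.

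| Design | Dropout | Improvement | False difference | Type I error |
|---|---|---|---|---|
| two arms | 15% v 5% | 0.5 SD | 0.05 SD | 5.4% |
| two arms | 15% v 5% | 1 SD | 0.10 SD | about 6.5% |
| two arms | 20% v 0% | 1 SD | 0.20 SD | 10.5 to 10.7% |
| two arms | 20% v 0% | 1.5 SD | 0.30 SD | about 17% |
| three-arm ANOVA | 10/10/10% | 1 SD | 0 | about 5% |
| three-arm ANOVA | 15/15/5% | 1 SD | 0.10 SD | about 6% |
| three-arm ANOVA | 5/5/20% | 1 SD | 0.15 SD | 7.7% |
| three-arm ANOVA | 20/20/0% | 1 SD | 0.20 SD | about 10% |

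In the three-arm rows the false difference is between the arm with the odd dropout rate and the other two. The 5/5/20% row averages (5 + 5 + 20)/3 = 10%, the article's own planning rate.

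**4. Power with equal dropout**

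With 0.44 read as Cohen's f, 28 per arm and no dropout, three-arm ANOVA power is about 95%. With 10% random dropout it is about 86 to 90% under baseline carried forward (mean improvement 1 SD to 0 SD) and about 93 to 94% using completers only.

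**5. What the per-protocol contrast can show**

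In the same simulations, analysing completers alone gives no false difference and about 5% type I error, because dropout was random. So if per-protocol excludes people without week-4 data, the contrast could expose the LOCF artefact in this special case. If dropout depends on the outcome, completers are a selected group and both analyses can be biased. The contrast then has no component that varies the assumption about the missing values.

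**The case against.** Five counter-arguments deserve an answer.

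- **LOCF may not be the main method.** This stands. An imputation approach is named beside it and may be defined in a fuller document. A reader might infer that LOCF is the sole or primary handling; the text does not establish that. But LOCF is a stated analysis, and it is unsuitable for these outcomes whatever its rank.
- **The contrast might reveal the artefact.** This also stands in part. A reader might infer that the planned sensitivity analysis could never show the problem. That fails when per-protocol drops non-completers and dropout is random, as step 5 of the working shows. The article does not define the per-protocol set, so this cannot be relied on.
- **Not every outcome has a single post-baseline visit.** Correct for JOA and MPQ over the whole schedule. It changes nothing for the EMG and biomarker outcomes or for week 4.
- **Unequal dropout is not shown.** True. The article gives one 10% rate, about 3 of 28 per arm (0.10 × 28 = 2.8). Supervised sessions five times a week and a daily oral drug are different burdens, so unequal loss is plausible. Qigong and MCE share the same session load, so that argument does not reach their comparison.
- **Baseline carried forward is conservative.** Not reliably. If a comparator arm loses more people, the bias favours Qigong.

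**Conclusion.** The point holds for all week-4 outcomes. That LOCF equals baseline carried forward follows from the schedule alone and needs no assumption. Its size does need assumptions. With random dropout, correlation 0.5 and a 1 SD improvement, moderate imbalance (15% v 5%) gives a false 0.10 SD and type I error of about 6 to 6.5%. Marked imbalance (20% v 0%) gives 0.20 SD and about 10 to 11%. Equal 10% dropout costs about a tenth of any true difference and does not inflate type I error. At the planned dropout rate the effect is therefore modest unless losses are clearly uneven. No figure in the article supports a particular improvement in the EMG measures, so larger illustrations such as 1.5 SD should not be taken as expected.

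The per-protocol versus intention-to-treat contrast is not a test of the missing-data assumption. It combines adherence and missingness and is uninformative about dropout that depends on outcome. This should be corrected before analysis.

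**What to change.** Amend the Statistical analysis section as follows.

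1. Remove LOCF for the week-4 outcomes.
2. State the main analysis: all randomised participants as assigned, in a baseline-adjusted model, with multiple imputation under missing at random. This also gives the undefined imputation step a content.
3. Replace the per-protocol versus intention-to-treat contrast, in its role as missing-data sensitivity analysis, with one that varies the assumption about missing values by arm. Delta-adjusted imputation is one option. The shifts should run in both directions, because the article states no direction of benefit for the EMG measures.
4. Keep per-protocol as a separate supportive analysis of adherence.

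No new data or visits are needed. The cost is revised wording and modest extra programming, including a choice of delta range for each outcome.

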### Quality assurance

Before agreeing to participate, it will be ensured that each participant meets tight eligibility requirements. All of the researchers have received professional training to understand how to carry out a typical research protocol and the operational requirements. Particularly, there will be individuals in charge of gathering and registering test information. Periodically, the data will be audited by the DMC monitors.

